#### Frailty

Will be assessed using a modification of the Fried assessment [43] based on low hand grip strength, low four meters average walking speed, low caloric expenditure on physical activity, self-reporting of extreme fatigue or low functionality and a spontaneous reduction of at least 4.5 kg in the past year. In this method, the low hand grip criterion is met when grip strength, assessed as the maximal result of 3 readings of the dominant hand by a handheld dynamometer [Jamar® Plus+ Digital Hand Dynamometer (Jamar® Smart) 200-lb.] is less than or equal to the gender- and body mass index–specific cutoff points provided by Fried et al. [43]. The slow gait speed criterion is met if the participant scored more than 4 s [44]. The 5-item FRAIL scale [45] which included the following 5 components: fatigue, resistance, ambulation, co-morbidity, and loss of weight. In both tools, frailty scores range from 0 to 5 (ie, 1 point for each component; 0 = best score, 5 = worst score) and are further categorized into: frail (3–5), pre-frail (1–2), and robust (0).

#### Functional tests

Other tests for functional ability using standardized protocols will be performed: time up and go test (TUG) [46], 30 s sit to stand (STS 30) [46], 30 s one leg stand [47], 2 min walk test [48], and isometric knee extension strength [49].

#### Glycemic control

FPG and HbA1c will be measured to evaluate metabolic control. At screening, Week 10 and Week 20 subjects will be asked to provide self-measured plasma glucose (SMPG) using blood glucose meters (see Table 1). SMPG is a measure of 7-time points: before breakfast; 120 min after start of breakfast; before lunch; 120 min after start of lunch; before dinner; 120 min after start of dinner; and at bedtime.

#### Ambulatory blood pressure monitoring

Twenty-four–hour ambulatory blood pressure (BP) monitoring (ABPM) will be measured with a fully automatic device (SpaceLabs 90207; Spacelabs Healthcare, Snoqualmie, WA). Daytime recordings are obtained every 20 min, whereas nighttime readings are collected every 30 min. BP variability (BPV) will be assessed as described elsewhere [50].

Sitting BP (diastolic and systolic) and pulse measurements will be preceded by at least 5 min of rest for the subject in a quiet setting without distractions (e.g. cell phones) and will be assessed in a sitting position with a completely automated device.

#### Nutritional intake

Based on the food records obtained by a registered nutritionist (AB) the total energy intake and the proportion of carbohydrates, proteins, and fats as well as several micronutrients will be calculated in the three interventional groups.

#### Quality of life

Will be self-reported and assessed by the SF-12 (a shorter version of the SF-36). The SF-12 yields two summary scores: physical component summary and mental component summary. The SF-12 is strongly correlated with the SF-36 [51]. The SF-12 have been translated and validated in Hebrew in inclusive studies of population aged 18–75 years [52].

#### Blood tests

Hormonal profile of each subject will be obtained at each study period and will include: LH, FSH, estradiol (E2), bioavailable and free testosterone, insulin, IGF-1 and 25-hydroxy vitamin D. FPG and HbA1C levels will be obtained from HMO’s records (up to 3 months before the study and at week 10 and 20). For future examinations frozen plasma and blood samples from patients will be stored and kept at − 20 °C and − 80 °C respectively.

#### Adverse events

An adverse event (AE) is considered as any unexpected and untoward event or medical occurrence in a participant that is related or not necessarily related to the treatment allocated in the study. AEs will be monitored in all study arms. Decision on the relation of event and the protocol will be made and documented. AEs will be classified by their severity (mild/ moderate/ severe), their causality (relation to the treatment: probable/ possible/ unlikely) and their outcome (resolved/ resolving/ resolved with sequelae – a lasting effect of the AE/ fatal). Every 2 weeks the subjects will be contacted by telephone and conduct an interview that will be documented in an AE log.

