**Methods:**

One hundred and twenty men and women ≥65 years of age with type 2 diabetes, and low levels of physical activity will be randomized (1:1:1 manner, gender stratified) for 10 weeks to one of 3 parallel arms: CRT consisting of 3 home sessions/week; ad-libitum plant-based Mediterranean diet (limited consumption of eggs, dairy and fish, avoidance of red meat and poultry) or empagliflozin 10 mg/day. After 10 weeks CRT will be added to the empagliflozin and diet arms for an additional 10 weeks. Allocation concealment and blinding of primary outcome assessors will be implemented. Efficacy will be determined by assessment of lean body mass, body weight, frailty and functional status, sarcopenia, HbA1c and quality of life questionnaires. Safety will be evaluated by routine monitoring of adverse events. This study was approved by the Tel-Aviv Sourasky Medical Center Institutional Review Board.

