#### Empagliflozin (SGLT-2 inhibitor)

Subjects allocated to empagliflozin will be asked to add empagliflozin 10 mg, preferably in the morning, to their medication regimen. Subjects will be monitored for adverse events including hypoglycemic events during all study visits.

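### The adverse event definition requires an event to be unexpected, which conflicts with the empagliflozin section and risks uneven recording between arms; the outcome scale has no code for a persisting event or an unknown outcome

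*Protocol article*

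**What the plan says.** The Abstract of the Protocol article rests the safety evaluation on adverse events: "Safety will be evaluated by routine monitoring of adverse events". The Adverse events section supplies the working rule. Its definition begins "An adverse event (AE) is considered as any unexpected and untoward event or medical occurrence in a participant" and continues "that is related or not necessarily related to the treatment allocated in the study". It then gives two short code lists, one for causality, "their causality (relation to the treatment: probable/ possible/ unlikely", and one for outcome, "their outcome (resolved/ resolving/ resolved with sequelae – a lasting effect of the AE/ fatal". On collection it says "AEs will be monitored in all study arms" and "Every 2 weeks the subjects will be contacted by telephone and conduct an interview that will be documented in an AE log".

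One treatment section carries its own safety instruction. Under Empagliflozin (SGLT-2 inhibitor) the article says "Subjects will be monitored for adverse events including hypoglycemic events during all study visits". The CRT and diet sections have no matching sentence.

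**The concern.** Expectedness is useful for sorting events that have already been recorded. Here it sits in the definition, where it decides whether an event is recorded at all. Taken literally, staff would log surprising events and could leave out the foreseeable ones, which are the events most likely to come from the treatments. The same article then treats one foreseeable event, hypoglycemia, as an adverse event.

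The comparison between arms is at stake. The trial sets three very different treatments side by side in people aged 65 and over, and an event that is foreseeable under one may be a surprise under another. If the entry rule depends on the arm, a difference in adverse event counts may partly reflect the rule. The code lists raise a second problem: an event that fits no code is left blank or given one that does not describe it.

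**Working it through.** No arithmetic in the plan bears on this point, so the check sets the passages side by side.

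**1. The definition.** There are two ways to parse it.
- *Unexpected* and *untoward* both qualify everything that follows. An anticipated effect of a treatment is then not an adverse event.
- The two adjectives qualify only *event*, and *medical occurrence* stands alone. Any medical occurrence then counts, and *unexpected* does no work for medical events.

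The first is the plain reading. The second is possible, but the two give different logs, and the text does not choose between them.

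**2. Definition against the empagliflozin section.** That section counts hypoglycemic events as adverse events. By naming them in advance, the article shows that it anticipates them. On the first parse the two sections conflict; on the second they agree. They need to be reconciled.

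**3. Which arms the empagliflozin sentence covers.** It stands under the drug heading. The inclusion criteria let participants take any antihyperglycemic agent other than an SGLT-2 inhibitor, whatever their arm, so hypoglycemia can also be foreseen in the diet and CRT arms. There, only the general definition governs.

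**4. Arm dependence.** Take muscle soreness as an illustration (the article's safety text does not mention it). During the first 10 weeks it would be expected under CRT and not under diet or drug. An expectedness condition would then drop it in one arm and keep it in two. Trial design describes the study as open label. The follow-up assessors that Blinding lists as blinded cover blood analysis, nutrition, eye examination, ambulatory blood pressure and quality of life; none is assigned adverse events. The study physician is listed as unblinded.

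**5. Outcome codes.** Set the possible states of an event at last contact against the four codes:

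| State at last contact | Code available |
|---|---|
| Over, no lasting effect | resolved |
| Over, with a lasting effect | resolved with sequelae |
| Ongoing, improving | resolving |
| Death | fatal |
| Ongoing, not improving | none |
| Unknown (for example after withdrawal) | none |

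Two of the six states have no code. Table 1 ends the CRT arm at week 10 and the other arms at week 20, and the article describes no later adverse event contact. If follow-up does stop there, an event starting in week 8 can be observed for 10 − 8 = 2 weeks in the CRT arm and 20 − 8 = 12 weeks in the others. The gap would then be met sooner in the CRT arm.

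**6. Causality codes.** There are three, the lowest being *unlikely*. The definition admits events not necessarily related to treatment, so an unrelated event is graded *unlikely*. Two low categories merge, but no event leaves the record.

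**The case against.** The best defence is that *unexpected* is loose wording and not a working filter. The article gives no list of expected events and no instruction to discard any. Treatment-related events are inside the definition and have a *probable* code. All arms receive logged two-weekly calls, and hypoglycemia is named for the drug arm. Table 1 also schedules vital signs, resting and 24-hour blood pressure and a diabetes diary, and the Glycemic control section adds self-measured glucose, so low readings can reach the data by another route. Trial design commits to Good Clinical Practices, and a full protocol or case report form may carry longer code lists.

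Much of this stands, and it limits the consequence. A reader might infer that the known harms of all three treatments fall outside the safety record, even up to all foreseeable treatment-related events. The documents do not support that. Hypoglycemia is expressly kept for the drug arm, a second parse exists, and there are no event rates from which to compute a loss. Nor do the documents show that every unresolved event lacks a code, since *resolving* covers those that are improving.

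The defence does not remove the defect. The definition and the code lists are stated text, not detail left to a fuller document. The absence of a list of expected events leaves the judgement to staff who may know the allocation. Nothing stated carries diary readings into the adverse event log.

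**Conclusion.** The point holds in a limited form. The definition, plainly read, conflicts with the empagliflozin section and exposes adverse event recording to differences between arms in what staff regard as expected. The outcome scale omits two states that can occur at last contact. The missing *not related* causality code is minor.

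The size of any loss or miscoding cannot be derived from the documents, and wholesale loss is improbable given the two-weekly calls in all arms. The conclusion about uneven recording assumes that staff apply the definition as written and know the allocation when they do; the article does not say who decides what enters the log. No efficacy endpoint, sample size, power or error rate is touched, and the trial calls itself exploratory. This is a moderate correction, not a condition for the trial to proceed. It is best made early, because events left out when they occur may not be recoverable.

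**What to change.** - In the Adverse events section, delete the words *unexpected and*, so that an adverse event is any untoward event or medical occurrence, related to treatment or not. Record expectedness as a separate attribute of each logged event.
- Add *not resolved/ongoing* and *unknown* to the outcome scale. Adding *not related* to the causality scale is optional.
- Reconcile the Adverse events and empagliflozin sections by stating that hypoglycemic events enter the same adverse event log in all three arms.

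The cost is a change of wording and two or three extra codes on the log. The downside is that somewhat more events will be recorded and reported. The change concerns recording only and alters no treatment or clinical rule.

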### Discontinuation

Participants may withdraw consent for any reason at any time or be discontinued from the trial by the investigator if based upon his clinical judgment, continuation in the trial is deemed inappropriate. In addition, a subject may be discontinued by the investigator if enrollment into the trial is inappropriate, the trial plan is violated, or for administrative and/or other safety reasons.

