##### Blinding

As mentioned we will use allocation concealment, such that at baseline all outcome assessors will be blinded to allocation. At follow up outcome assessors that will be blinded to the participants allocation will include: laboratory technicians (performing blood analysis); research assistant (AL) (in charge of nutritional analysis and the Med-diet questionnaire); ophthalmologist (for eye examination); endocrinologist (YM) (analyzing the 24–hour ambulatory blood pressure monitoring [ABPM]); another researcher (AD) (analyzing the quality of life questionnaires). The study physician (RE), nutritionist (AB), physiologist (OK) and physical instructor (AR) will not be blinded due to their role of instructing the patients on the intervention as well as collecting the following outcomes: body composition (automatic analysis but measured by AR); food intake and RMR (AB) and physical performance tests (OK).

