#### Analysis

##### Data confidentiality

This is an investigator initiated unblinded study. Personal medical data will be available to the investigators. During data analysis and for presentation and publication purposes data will be anonymized.

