Primary analysis will be intent to treat analysis. It will include all patients that had been randomized, started protocol and reached the end of the trial examinations (or last observation available will be imputed as their “end of study value”). Per protocol analysis will be performed by the a-priori conditions: a) for participants who had high compliance to workout (≥ 2/3 of sessions); b) for participants who had high compliance to diet (≥ score 9 in the Med-diet score and/or caloric consumption change from baseline was not more than 15% of report at baseline); c) for participants who had high compliance to drug therapy (≥80% tablets taken); d) for participants who did not violate the protocol (for example: changed thier habitual diet in the CRT arm; initiated new physical activity other than the one prescrived by us, ect.).

Sensitivity analysis can include all the participants who finished the trial including dropouts, with imputation of the last observation. This will be compared to an analysis which includes only participants that fully completed the study (have an assessment at the end of study).

We may also perform a mixed model for repeated measurements based on assessments of participants who completed the study and had high compliance to the treatment. An unstructured covariance matrix for measurements within the same participant will be employed, assuming that measurements for different participants are independent. The covariates and factors in Table 2 will be nested in the model.

Last, subgroup analysis will be done by stratification to several factors shown in Table 2, where ANCOVA or logistic regression models will be performed according to the outcome assessed (Table 3).

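### Plan violation is a stated ground for removing a participant from the trial, which works against the intent-to-treat primary analysis and per-protocol condition (d)

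*Protocol article*

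**What the plan says.** **Discontinuation.** Participants may withdraw consent, or "be discontinued from the trial by the investigator if based upon his clinical judgment" continuing is thought inappropriate. The next sentence adds further grounds: "a subject may be discontinued by the investigator if enrollment into the trial is inappropriate, the trial plan is violated", followed by administrative and other safety reasons. Plan violation is thus listed separately from clinical judgment, safety and consent. The section does not define it.

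**Who decides.** Data confidentiality states: "This is an investigator initiated unblinded study". Blinding says that the study physician, nutritionist, physiologist and physical instructor "will not be blinded due to their role of instructing the patients on the intervention".

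**Analysis (text under Baseline comparisons).** "Primary analysis will be intent to treat analysis". The set is then described: "It will include all patients that had been randomized, started protocol and reached the end of the trial examinations", or else the "last observation available will be imputed as their" end-of-study value. Per-protocol condition (d) is an analysis "for participants who did not violate the protocol". Its examples are a CRT participant who changes habitual diet and a participant who takes up other physical activity. Conditions (a) to (c) deal with adherence to training, diet and drug.

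**Measurement times.** In Table 1 the body weight and BIA rows are marked only at baseline, week 10 and week 20. The CRT arm finishes at week 10.

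**The concern.** An intent-to-treat comparison needs outcomes from participants whatever they did after randomisation. Per-protocol condition (d) differs from it only if violators stay in the trial and are measured. The Discontinuation section allows those same people to be taken out first, by staff who know the arm and on the basis of conduct after randomisation. A week 10 or week 20 outcome that could have been obtained may then be replaced by an imputed one.

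The imputed value carries no information about the period of interest. With no weight or BIA measurement between baseline and week 10, the carried-forward change for anyone removed in that interval is exactly zero. For a removal between weeks 10 and 20 in the diet and drug arms, the week 10 value stands in for week 20. Either is wrong whenever the participant's weight or lean mass did change. The kinds of violation named in the article, a changed diet or extra activity, are ones that could plausibly change them.

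**Working it through.** **The plan's own figure.** The Sample size section assumes a 3.2 kg difference in weight at week 10 between the empagliflozin and CRT arms, no change in the CRT arm, 80% power, a 5% level and 40 per arm. It states no SD for weight, so the 40 cannot be reproduced; only the implied SD can be found. Taking the test as two-sided (sidedness is not stated):

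- Normal approximation: SD = 3.2 × √20 / (1.960 + 0.842) = 5.1 kg.
- Noncentral t: SD = 5.04 kg.

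**Inputs for the illustration.** From the article: 40 per arm, 3.2 kg, no mean change in the CRT arm, and last-observation imputation with weight measured only at baseline, week 10 and week 20. Assumed: the number removed before week 10 and the weight change of those removed. The article gives neither. Four of 40 is 10%; this equals the attrition the article allows for, but that figure is not a forecast of removals for violation. The illustration is in kg because the sample size is; the primary endpoint is percentage change.

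**Contrast (drug loss minus CRT loss), 4 of 40 removed from one arm:**

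| Removed | True contrast, all 40 measured | Primary analysis (zero carried forward) | Completers only |
|---|---|---|---|
| CRT participants who changed diet and lost 3.2 kg each (assumed) | 3.2 − (4 × 3.2 / 40) = 3.2 − 0.32 = 2.88 kg | 3.2 − 0 = 3.2 kg | 3.2 kg |
| Drug-arm participants with the full 3.2 kg effect | 3.2 kg | 36 × 3.2 / 40 = 2.88 kg | 3.2 kg |
| Drug-arm participants who lost no weight, the other 36 losing 3.2 kg | 36 × 3.2 / 40 = 2.88 kg | 36 × 3.2 / 40 = 2.88 kg | 3.2 kg |

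- Row 1: the primary analysis overstates the contrast by 3.2 / 2.88 = 1.11, or 11%. With 2 removed it is 3.2 / 3.04 = 1.05; with 8 removed, 3.2 / 2.56 = 1.25.
- Row 2: the primary analysis understates it by 10%. With 2 removed it reads 3.04 kg (5% low); with 8 removed, 2.56 kg (20% low). At the implied SD of 5.04 kg and 40 per arm, power falls from 80% to 76%, 71% and 61% for 2, 4 and 8 removed. This is an upper bound on the dilution if removed participants would have lost no more than the full mean effect.
- Row 3: the primary analysis is unbiased. Only the completer analysis, which the article lists as a sensitivity comparison, is overstated, by 11%.

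The error in the primary analysis therefore runs up, down or not at all, depending on which arm is affected and what the removed participants' weight did.

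**The case against.** **The wording is permissive and generic.** The rule says that the investigator may discontinue, so loss of data is a risk and not a stated consequence. A discretionary power can coexist with intent-to-treat and per-protocol analyses: violators who are kept go through condition (d), and those removed go through imputation, which the article expressly plans. This stands. The two sections are in tension; they do not formally contradict each other. It does not dispose of the point, because imputation cannot recover an outcome that could have been measured.

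**A condensed article may leave follow-up after discontinuation to the full protocol.** This also stands, and the absence of such a rule is not the complaint. The complaint is about a ground for removal that the article does state.

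**Stronger readings that the documents do not support.** A reader might infer that poor adherers will be removed. Nothing in the article says so: Measures of compliance/adherence only classifies adherence, and the per-protocol list keeps adherence (a to c) apart from violation (d). A reader might also infer that removing drug-arm participants who did not respond inflates the primary effect by 5% to 25% and turns it into a comparison of adherers. Row 3 of the table shows why not: zero is then the correct value, and the primary estimate equals the true mean. That inflation belongs to the completer analysis.

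**Conclusion.** The point holds in a limited form. The article allows an unblinded investigator to end trial participation because the plan was violated, while its primary analysis and its per-protocol condition (d) both need violators to be kept and measured. The power serves no analytic purpose, since condition (d) already sets violators aside.

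The size cannot be estimated from the document. With 4 of 40 removed from one arm before week 10, the primary drug-CRT contrast could read 3.2 kg when 2.88 kg is true, 2.88 kg when 3.2 kg is true, or be correct. No single direction of bias can be claimed.

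These figures rest on the assumed number removed, on their assumed weight change, and on baseline counting as the last available observation. If baseline does not count, removed participants drop out and the primary analysis behaves like the completer column. The matter deserves a change of wording; it does not undermine the design.

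**What to change.** Reconcile the Discontinuation section with the analysis text:

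1. Delete violation of the trial plan as a ground for leaving the trial.
2. Record violations as they occur, for use in per-protocol condition (d).
3. State that participants who violate the plan or stop the assigned intervention are still invited to the scheduled week 10 assessment and, in the diet and drug arms, the week 20 assessment, unless they withdraw consent for follow-up.

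The clinical and safety grounds stay exactly as they are. The cost is one paragraph of wording and a few visits that are already in the schedule.
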